#### Exclusion criteria

Patients with serious life-threatening diseases and critically ill patients of post-COVID-19 syndrome will be excluded. Pregnant females and lactating mothers will not be considered for the study. Patients who will be unfit for *Basti* will be excluded from the study. Patient who has known hypersensitivity reactions to medicines mentioned in the study will be excluded. Any other patient whom investigator feels not to be included will be excluded from the study.

#### Withdrawal criteria

During the course of this treatment, if any serious condition or emergency condition develops, the required treatment will be given immediately to patients and such subject may be withdrawn from the study. Noncompliance patients will be withdrawn from the study. Patients selected for this study who are not following instructions properly will be considered as dropout.

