**Assessments**						
Concomitant illness	×	×	×	×	×	×
Complete physical examination	×	×	×	×	×	×
Signs and symptoms assessment	×				×	×
Assessment of vitals	×	×	×	×	×	×
Ayurvedic evaluation	×	×	×	×	×	×
*Basti* charting				×		
Clinical scales assessment	×				×	×
Study drug dispensation		×	×	×	×	
compliance			×	×	×	×
Fatigue severity scale	×				×	×
MMRC dyspnea scale	×				×	×
Chest pain scale	×				×	×
VAS	×				×	×
Smell and taste scale	×				×	×
WOMAC Scale	×				×	×
Hamilton depression scale	×				×	×
Hamilton anxiety scale	×				×	×
Insomnia Severity Index	×				×	×
Cough Severity Index	×				×	×
Facial aging scale	×				×	×
Dizziness scale	×				×	×
Pittsburgh severity quality index	×				×	×
Functional status scale	×				×	×
Heart palpitation scale	×				×	×
Completion and outcome						×

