### Study design

This is a prospective, open-labeled proof of concept pragmatic study. The study duration is 18 months, and the intervention period is 35 days from the day of enrollment of the patients. The trial will be conducted at OPD, IPD of Kayachikitsa, Casualty and Periphery of Government Ayurved College and Hospital, Nagpur. Clinical assessment and Ayurveda-based clinical assessment will also be carried out. The detailed flow chart of process is shown in Fig. 1.

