### Monitoring

At zero day, the participants will be physically checked by the study physicians at all visits till the completion of the study. At all time points, assessment of participants will also include in-depth inquiry of possible symptoms of COVID-19 in the family members and close associates. The daily response of the participant will be seen by the physician and study co-ordinators. In addition, a telephonic contact will be made with the participant by the coordinator once in every week till the completion of the study to find out about any matter concerning health, adverse event, or the study. The schedule of enrollment, interventions, and assessments is provided in Table 1.

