#### Intervention arm (Group 1)

The *Santarpanottha* group will be treated in three stages: *Pachan, Shodhan,* and *Rasayan* in a sequence as follows:
*Pachan*
* (*conversion of toxins in removable form)—Ayurveda formulation *Guggulutiktak Kashaya* 10–30 ml BD orally after meals with warm water and *Gomutra arak* (cow urine distillate) for 3 to 5 days will be given. *Guggulutiktak Kashaya* is a classical Ayurvedic decoction used to treat diseases arising from over nutrition.
*Shodhan* (removal of toxins)—Classical *Ayurveda Yog Basti* treatment includes 8 days of per rectal medications as per classical Ayurved methods, i.e., *Anuvasan Basti* and *Niruh Basti* will be administered on alternate days. Processed sesame oil will be used for *Anuvasan Basti* 60–100 ml per rectally after meal OD given for alternate 3 days, and *Triphala* decoction mixed with processed sesame oil and cow urine distillate will be used for classical *Niruh Basti*. The dose of *Niruha Basti* will vary between 400 and 850 ml empty stomach OD given for alternate 3 days. The last two *Basti* will be *Anuvasan* that is processed sesame oil after meal. One will be given either *Anuvasan* or *Niruha* on alternate days from the 1st to 6th day. In the last 2 days, i.e., the 7th and 8th day, *Anuvasan* will be given.
*Rasayan* (rejuvenation)—After completion of classical *Yog Basti* treatment, *Rasayana* treatment will be given for 21 days. *Brahma Rasayana* will be used as a *Rasayana* in the dose of 10–30 g OD orally on an empty stomach in the morning with warm water for 21 days.

The exact dose for each patient will be finalized on the basis of Ayurveda-based parameters like *Koshtha*, *Agni*, and *Basti Nirgaman*.

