#### Intervention arm (Group 2)

The *Apatarpanottha* group will also be treated in three stages: *Pachan, Shodhan, and Rasay*an in sequence as follows:
***Pachan*** (conversion of toxins in removable form)—Ayurveda formulation Tablet Laghumalini *Vasant* 250–500 mg BD orally after meals with water for 3 to 5 days.
***Shodhan*** (removal of toxins)—*Yog Basti* treatment includes 8 days of per rectal medications as per classical Ayurved methods, i.e., *Anuvasan Basti* and *Niruh Basti* will be administered on alternate days. *Kshirbala oil* will be used for *Anuvasan Basti* 60–100 ml per rectal after meal OD for 5 days. Milk processed in *Brihat Panchmula herbs* will be used for *Niruha* per rectal in dose 400–850 ml on an empty stomach OD given for alternate 3 days. One will be given either *Anuvasan* or *Niruha* on alternate days from the 1st to 6th day. The last 2 days, i.e., the 7th and 8th day, *Anuvasan* will be given.
***Rasayan*** (rejuvenation)—After completion of classical *Yog Basti* treatment, *Rasayana* treatment will be given for 21 days. *Kalyanak Ghrit* will be used 15–30 ml OD orally on an empty stomach in the morning with warm water for 21 days.

The exact dose for each patient in both groups will be finalized on the basis of Ayurveda-based parameters like *Koshtha, Agni*, and *Basti Nirgaman* (evacuation).

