### Adverse events

All adverse events (AEs) during the therapy will be recorded and monitored as per ICH-GCP (2016) [15] and ICMR guidelines [16]. The safety of the participants would also be assessed in case of all withdrawals. All adverse events will be recorded and followed till resolution. All adverse events will be classified by the study physician and recorded in the AE form. The Data Safety Monitoring Board (DSMB) will be formed to monitor the safety of the participants and assess the safety data. Clinical assessments will be carried out as per Table 1.

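### The withdrawal rule lets a patient with a serious or emergency condition leave the study, not just the treatment, so the Day 35 scales can be lost

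*Protocol article*

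**What the plan says.** Withdrawal criteria in the protocol article covers a serious or emergency condition arising during treatment. In that case "the required treatment will be given immediately to patients and such subject may be withdrawn from the study". The wording permits withdrawal without requiring it, and gives no criterion for deciding. It names no intermediate state in which study treatment stops while follow-up continues.

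For patients who are withdrawn, Adverse events provides a safety check: "The safety of the participants would also be assessed in case of all withdrawals". It also follows adverse events until they resolve. It does not mention the efficacy scales.

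In Table 1 the row "Clinical scales assessment", like the rows for the individual scales, is marked at screening, in the Days 14 to 34 column and at Day 35. There is no assessment for withdrawn patients.

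Study design states: "This is a prospective, open-labeled proof of concept pragmatic study". Both treatment groups are headed as intervention arms. Monitoring adds: "The daily response of the participant will be seen by the physician and study co-ordinators".

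**The concern.** Leaving the study and stopping the study medicines are different things. A patient who has a serious event may have to stop treatment, but the Day 35 scales can often still be taken. As worded, the rule allows collection to end with the treatment, and a score never collected cannot be recovered by any later analysis plan.

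The design makes this matter more. The objectives concern change over 35 days within each group, and the within-patient tests named under Analysis (Wilcoxon signed-rank, paired t) need a baseline and a follow-up value. No untreated arm exists against which losses could be compared. Patients with serious events during treatment are unlikely to be a random subset. The study is open-label and staff see each patient's response daily, so the discretionary decision can be made with that response known. If these patients drop out of the Day 35 comparison, the reported change describes those who remained and not those who were enrolled.

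**Working it through.** The plan gives no figure on this point to reproduce. Its total of 24 patients has no stated standard deviation or formula behind it, and the point does not depend on it. Two things can be worked out: what the schedule fixes, and what one lost patient does to a mean.

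**1. When a withdrawn patient has no post-baseline score**

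- Oral preparatory course: 3 to 5 days. Enema course: 8 days (both from the two intervention-arm sections).
- End of the enema course: 3 + 8 = Day 11 at the earliest, 5 + 8 = Day 13 at the latest.
- First post-baseline scales: somewhere in Days 14 to 34 (Table 1).

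Both courses therefore end before any post-baseline scale is due. Withdrawal on any of Days 1 to 13 leaves a baseline only.

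There are 34 days (Days 1 to 34) before the completion visit. If the interim scales are taken on day *a*, the share of those days with no post-baseline score yet is (*a* - 1)/34:

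| Interim scales on | Days without a score | Share |
|---|---|---|
| Day 14 | 13 of 34 | 38% |
| Day 24 | 23 of 34 | 68% |
| Day 34 | 33 of 34 | 97% |

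These are shares of calendar time, not probabilities of an event. A patient withdrawn after the interim assessment loses Day 35 but keeps one post-baseline score.

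**2. Effect of one patient with no usable score**

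Inputs: the other patients average a 40% reduction (planning figure, Sample size and power). The lost patient would have had a reduction of *d*%, which is an assumption; a negative value means worsening. *n* is 24 in total, or 12 per group if the groups are equal, also an assumption.

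- Mean over everyone: ((*n* - 1) × 40 + *d*)/*n*
- Mean over those observed: 40
- Shift from the loss: 40 minus the first line = (40 - *d*)/*n*

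| *d* | *n* = 24 | *n* = 12 |
|---|---|---|
| -20 | 60/24 = +2.5 | 60/12 = +5.0 |
| 0 | 40/24 = +1.7 | 40/12 = +3.3 |
| 60 | -20/24 = -0.8 | -20/12 = -1.7 |

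Units are percentage points; a plus sign means the reported improvement is too large.

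If an interim score *s* stands in for the missing Day 35 score, the shift becomes (*s* - *d*)/*n*. It is zero when the two are equal.

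**The case against.** The strongest reply is that this is a condensed article and that the clause is permissive. It does not say that data collection stops, and a full protocol could provide for assessment after withdrawal. That is true. But the article does state the conduct rule, the exit it names is from the study, and the follow-up it specifies for withdrawals concerns safety. The wording permits the loss even though it does not compel it.

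Second, the events should be rare. Exclusion criteria state: "Patients with serious life-threatening diseases and critically ill patients of post-COVID-19 syndrome will be excluded". Participation lasts only 35 days. This stands and limits the importance of the point.

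Third, withdrawal under this clause needs a serious or emergency condition first, so poor response alone is not a trigger. This also stands. Knowledge of the response can affect only the discretionary step that follows the event.

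Fourth, the sample size allows for 20% dropout. That protects the number of patients but does not make those who remain representative.

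Fifth, the illustration rests on chosen values of *d*, uses a mean where rank tests are planned for subjective criteria, and has no standard deviation to set the shift against. This is fair: the figures show scale only.

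Sixth, a Day 35 score after emergency care may partly reflect that care, and some would not want it in the analysis. That is a reason to decide openly how to use the score, not a reason to leave it uncollected.

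Finally, the next sentence of the same section makes withdrawal mandatory for non-compliance, which is the stronger form of the same problem. The present point is confined to serious and emergency conditions and does not cover it.

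**Conclusion.** The point holds. The withdrawal rule allows Day 35 outcomes to be lost for patients with a serious or emergency condition, and nothing else in the article retains them. The loss is complete if withdrawal comes before the interim scales, which covers at least Days 1 to 13 and so both the oral preparatory and the enema courses. After that, an interim score remains.

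The size and direction of any bias are unknown. On the stated assumptions, one patient without a usable score shifts the mean change by between -0.8 and +2.5 points in 24 patients, or between -1.7 and +5.0 in 12. It should be corrected because the remedy is cheap and the lost data cannot be recovered. Confidence is moderate, since few such events are expected and the full protocol is not at hand.

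**What to change.** Amend Withdrawal criteria to say that stopping study treatment after a serious or emergency condition is a clinical decision that does not end participation. State that the Day 35 scales are taken in every enrolled patient who can be assessed, unless consent is withdrawn, and that these observed scores enter the before-after analysis.

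The cost is one or two sentences and some extra follow-up effort for a visit already scheduled. There are three drawbacks: some scores may partly reflect the emergency treatment, some patients may be too ill to be scored, and the estimate may be less favourable.

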### Recruitment, screening, and consent

The participant of the age group 18–70 years will be selected for study. The study will include up to completion of 24 participants.

The investigator number 2 (PR) will be responsible for obtaining written informed consent from each participant prior to screening as per the national ethics guidelines [15]. An information sheet or case record format in a language best understood by the participant, giving details of the study, will be provided to the participant. Enough time will be given to the participant to make a voluntary decision to participate. The participant will be encouraged to ask questions and clear all doubts in a face-to-face interview with the investigator. After that, the participant will be asked to sign the consent form for the study research. The participants will be screened from the patients with post-COVID-19 syndrome complaints comprehensively by the study physicians for eligibility and to exclude any contraindication to participation in the study. If found eligible, the participants will be enrolled. The participants will be followed up at predetermined time endpoints (five visits including screening and completion visits) as per protocol till study completion (35th day). A detailed procedure is summarized in Fig. 1 and Table 1. Data will be recorded in case record form and will be then entered in an Excel sheet.

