### Statistical analysis

#### Sample size and power

The sample size for the study is calculated by using the formula with assumption which is made after the pilot study on 4 patients. The assumption made is that our treatment will reduce total symptoms by at least 40% with 95% confidence interval (*α* = 0.05) and 80% power of the study and expecting a dropout rate of 20%. Hence, a total of 24 patients will be recruited.

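### Withdrawing non-compliant patients from the study, not only from treatment, ends their outcome data and is likely to flatter an uncontrolled before-after result

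*Protocol article*

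**What the plan says.** All places are in the protocol article.

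- **Withdrawal criteria.** "Noncompliance patients will be withdrawn from the study". The section adds: "Patients selected for this study who are not following instructions properly will be considered as dropout". The first rule is unconditional. For patients who develop a serious or emergency condition, by contrast, the section makes withdrawal only a possibility.
- **Adverse events.** Safety is to be assessed in all withdrawals. No section says that efficacy scales continue after withdrawal.
- **Table 1.** The clinical scales are taken at screening (Day 0), within Days 14 to 34, and at Day 35. None is scheduled between Day 1 and Day 13.
- **Analysis.** The within-patient tests are the Wilcoxon signed-rank test and the paired t test. No analysis set is named.
- **Study design.** "This is a prospective, open-labeled proof of concept pragmatic study".
- **Sample size and power.** The assumption is that "our treatment will reduce total symptoms by at least 40% with 95% confidence interval", with "80% power of the study and expecting a dropout rate of 20" per cent. "Hence, a total of 24 patients will be recruited".

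**The concern.** The rule joins two events that should be kept apart: stopping the study medicines and leaving the study. Compliance is judged after enrolment and during treatment, so the rule selects patients on something that happens after baseline. Someone who stops following the regimen during the oral or enema phase leaves before any post-baseline scale is due.

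In a randomised trial such losses would at least be visible against a comparator. Here patients are assigned to one of two active regimens by symptom type, and both objectives concern efficacy within a group. The before-after change in those who remain is therefore nearly the whole efficacy result, and selective loss feeds straight into it.

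A pragmatic question is usually about everyone started on the treatment. A result resting mainly on compliant patients answers a narrower one.

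A later analysis plan can choose who is analysed, but it cannot recover Day 35 scores that were never collected.

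**Working it through.** **1. The plan's own figure.** The total of 24 can be neither reproduced nor refuted, because no standard deviation (SD), formula or reference rate is printed. Two routes reach it:

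- 19 evaluable patients: 19 / (1 − 0.2) = 23.75, rounded up to 24.
- 20 evaluable patients: 20 × 1.2 = 24.

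Either way the plan allows for losing 24 − 19 = 5 or 24 − 20 = 4 patients.

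**2. What data a withdrawn patient has (Table 1).**

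| Time of withdrawal | Scale values available | Usable in a baseline to Day 35 paired test |
|---|---|---|
| Before Day 14 | Screening only | No |
| Days 14 to 34 | Screening, and at most one interim value | No, unless the interim value is substituted |
| Not withdrawn | Screening, interim, Day 35 | Yes |

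**3. Size of the possible bias.** Let d be the share of enrolled patients lost, c the mean change in those who remain, and x the mean change that those lost would have shown.

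- Mean over all enrolled = (1 − d) × c + d × x
- Overstatement = c − [(1 − d) × c + d × x] = d × (c − x)

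Inputs: d = 0.20 and c = 40% come from Sample size and power. The value of x is not in the document and is varied. It is also assumed that completers achieve the planned 40% and that the whole 20% is lost to follow-up.

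| x in those lost | Mean over all enrolled | Overstatement (points) |
|---|---|---|
| 0% | 0.8 × 40 + 0.2 × 0 = 32% | 8 |
| 10% | 32 + 2 = 34% | 6 |
| 20% | 32 + 4 = 36% | 4 |
| 40% | 32 + 8 = 40% | 0 |
| 50% | 32 + 10 = 42% | −2 |

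**4. Sensitivity to the share lost.** For x from 0% to 40%:

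- d = 0.10: overstatement 0.10 × 40 = 4 points, down to 0.
- d = 0.30: overstatement 0.30 × 40 = 12 points, down to 0.

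Rounding to whole patients changes little. With x = 0%, 19 of 24 remaining gives 40 × 19/24 = 31.7%, and 20 of 24 gives 40 × 20/24 = 33.3%.

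**The case against.** **Direction.** The protocol has no data on how non-compliant patients fare, so a flat statement that the rule inflates the result goes too far. This stands. The bias is the expected one if they improve less, and the last row of the table shows it reversing if they improve more.

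**Selection on response.** The Compliance section bases compliance on medication logs, returned containers, quantity consumed and patient-completed forms, not on symptoms. The Monitoring section has the physician and co-ordinators see the daily response in an open-label study, but nothing says that response informs who is withdrawn. A reader might infer that poor responders will be removed deliberately. The text does not support that. What remains is that non-compliance may itself be related to outcome.

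**Attribution.** The 20% is given without causes, and withdrawal for serious conditions is also allowed. The share due to this rule is unknown, so the illustration bounds all planned loss, not this rule alone. This stands.

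**Unseen documents.** Analysis sets and missing-data rules commonly sit in a fuller protocol or an analysis plan. So it cannot be said that the protocol prescribes a completers-only analysis, and an interim value may exist for late withdrawals. But the rule that ends participation is printed here, and it governs what is collected.

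**The pragmatic label.** The same sentence says proof of concept, and the objectives speak of efficacy. There is tension with the label, not a contradiction.

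**Conclusion.** The concern holds as a defect of stated text. The withdrawal rule ends outcome collection for non-compliant patients in an open-label study without a control, and this cannot be repaired afterwards. If the full 20% is lost and completers improve by 40%, the before-after change would overstate the all-enrolled mean by 8 to 0 percentage points as the change in those lost runs from 0% to 40%. The direction rests on the assumption that those lost do no better than those who remain.

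Two stronger readings should not be drawn:

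- A reader might take "The study will include up to completion of 24 participants" (Recruitment, screening, and consent) to mean 24 completers with dropouts replaced, in conflict with 24 recruited. The wording is awkward, but it also reads naturally as recruiting until 24 are included, and replacement is mentioned nowhere.
- A reader might say that a mean of 32% misses a 40% target. The 40% is a sample-size assumption, and the protocol sets no success criterion.

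**What to change.** 1. In Withdrawal criteria, separate stopping study treatment from leaving the study. Non-compliance should be recorded and should not by itself end outcome assessment. This leaves untouched the clinical decision on who stops treatment.
2. Collect the Day 35 scales on every enrolled patient who has not withdrawn consent.
3. Make the main analysis all enrolled patients who started treatment.
4. Report compliant patients only as a sensitivity analysis.

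The cost is a change of wording and a few extra Day 35 assessments: at most 4 or 5 if losses match the planned 20%, and fewer if some of those patients withdraw consent. The estimate may come out less favourable, but it would describe the patients who were actually started on treatment.

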### Monitoring

At zero day, the participants will be physically checked by the study physicians at all visits till the completion of the study. At all time points, assessment of participants will also include in-depth inquiry of possible symptoms of COVID-19 in the family members and close associates. The daily response of the participant will be seen by the physician and study co-ordinators. In addition, a telephonic contact will be made with the participant by the coordinator once in every week till the completion of the study to find out about any matter concerning health, adverse event, or the study. The schedule of enrollment, interventions, and assessments is provided in Table 1.

